## Methods

### Primary objective

The primary aim of this study is to determine the effectiveness of oral functional fatty acids in facilitating the expulsion of small gallbladder stones. Upon trial conclusion and researcher and participant unblinding, the pre and postintervention ultrasound examination data will be meticulously analyzed to comprehensively compare the expulsion volume and expulsion rate of gallbladder stones between the experimental group and the control group on the third and sixth days after the intervention through in-depth intergroup comparisons. Moreover, we will perform a detailed analysis of the differences in the expulsion volume and expulsion rate of gallbladder stones within the experimental group to compare the outcomes after a six-day intervention with those after a three-day intervention; relevant data from the control group will be subjected to the same in-depth intergroup analysis.

We hypothesize that the stone expulsion rate among patients in the experimental group who will consume functional fatty acids for 3 days, will be significantly greater than that among patients in the control group who will take placebo over the same period. Additionally, we anticipate that the stone expulsion rate of the experimental group patients who will take functional fatty acids for 6 days will exceed that of the control group patients who will receive placebo supplemented with functional fatty acids. Furthermore, when the experimental group and the control group are compared, the volume of gallstones expelled and the expulsion rate following a six-day intervention are expected to be notably greater than those observed after a three-day intervention.

### Secondary objectives

In this study, relevant indices, including the volume of the gallbladder and the thickness of the gallbladder wall, will be compared among patients via ultrasound examinations before and after the intervention. The purpose of this study is to determine whether the intervention affects gallbladder contraction function and can alleviate gallbladder inflammation.

Moreover, we will compare the rates of clinical adverse events, such as abdominal pain and diarrhea, before and after the intervention. This comprehensive comparison will help us gain a more in-depth understanding of the impacts and safety implications of the dietary therapy studied in this trial.

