### Eligibility criteria

Our target population comprises patients whose electronic medical records revealed small gallstones (defined as gallstones with a diameter less than 2 mm) and who underwent gallbladder ultrasound examinations at this hospital.

Inclusion criteria. (1) Adult patients who were diagnosed with small gallbladder stones (maximum diameter < 2 mm) via ultrasound and had no prior treatment history. (2) Patients of either sex, aged between 18 and 70 years, who were willing to participate in this study.

The exclusion criteria were as follows: (1) age <18 years or >70 years. (2) History of endoscopic retrograde cholangiopancreatography [ERCP]. (3) Previous gallstone removal surgery with gallbladder preservation. (4) History of acute or chronic pancreatitis or cholangitis. (5) Mirizzi syndrome. (6) History of gastrointestinal surgery. (7) Gastrointestinal obstruction. (8) Dysfunction of the sphincter of Oddi. (9) Gallbladder neck polyps. (10) Abnormal gallbladder structure (e.g., the gallbladder has multiple folds). (11) Gallbladder mass. (12) Common bile duct stones, extrahepatic biliary tract stones, or active biliary tract infection. (13) Congenital biliary abnormalities. (14) Biliary injury or surgery. (15) Biliary tumors. (16) Gastrointestinal bleeding, liver cirrhosis, or other malignant diseases. (17) Significant arrhythmia, bradycardia, or atrioventricular block. (18) Severe hypertension or liver or kidney insufficiency. (19) Immune, endocrine, hematological, or mental disorders. (20) Severe cerebrovascular disease. (21) Allergy to relevant foods. (22) Pregnant or breastfeeding women. (23) Unwillingness or inability to consent to participate.

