### Intervention description

Data pertaining to the small gallstones will be extracted from the electronic medical records of outpatients who underwent gallbladder ultrasound examination at this hospital. Follow-ups will be conducted via telephone. If a patient meets the inclusion and exclusion criteria, expresses willingness to participate, and has no clinical symptoms related to gallstones, a gallbladder ultrasound will be repeated by a trained and experienced sonographer. Only patients with gallstones measuring less than 2 mm at this follow-up examination will be eligible for enrollment. Eligible patients will be randomly assigned to the experimental group or the control group. The attending physician will explain the potential risks and benefits of the intervention, and written informed consent will be obtained from all participants.

The patients in the experimental group will take 50 mL of oral functional fatty acids on an empty stomach every morning for 6 consecutive days. In the control group, patients will first receive oral placebos for 3 days, followed by the same dose of oral functional fatty acids as the experimental group for the next 3 days. The blinded ultrasound physicians will perform gallbladder ultrasounds on the 3rd and 6th days after treatment to evaluate the effect of small gallstone expulsion. We chose the 3rd and 6th days after the intervention as the observation time points for evaluating the effect of small gallstone expulsion for the following reasons. On the basis of our experience and data from pilot studies, after 6 days of oral functional fatty acids, small gallstones were effectively expelled or exhibited a reduction in their content. However, it remains unclear whether the small gallstones were expelled precisely on the 6th day of intervention or before. Therefore, using the median value as a reference, we aimed to identify an optimal time point for evaluating the expulsion of small gallstones. Well-trained volunteers will follow up with patients during treatment to increase patient compliance and facilitate timely recording and management of any complications.

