#### Standardized ultrasound assessment protocol

All ultrasound examinations will be performed using a Philips EPIQ 7 ultrasound system with a 3–5 MHz convex array probe, following a standardized protocol. Patients will be examined in the supine and left lateral decubitus positions after an 8-h fast.

*Image evaluation*: All images will be independently reviewed by two board-certified sonographers with ≥10 years of experience in abdominal ultrasound, who are blinded to group assignments and previous examination results.*Disagreement resolution*: Any discrepancies between the two reviewers will be resolved by a third senior sonographer, whose decision will be final.*Image storage*: Both static images (at least 2 images per examination, including longitudinal and transverse views of the gallbladder) and dynamic video clips (5–10 s per view) will be stored in a secure digital repository for future review and quality control.

Measurement standardization:

*Gallstone number*: Counted in multiple views to ensure all stones are identified*Maximum stone diameter*: Measured in three orthogonal planes, with the largest value recorded*Gallstone volume*: Calculated using the ellipsoid formula: Volume = (*π*/6) × length × width × depth*Gallbladder volume*: Calculated using the ellipsoid formula: Volume = 0.52 × length × width × depth*Gallbladder wall thickness*: Measured at the anterior wall of the gallbladder in the longitudinal view, avoiding the neck and fundus regions

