#### Secondary outcome measures

Table 1 presents detailed information on the secondary outcome measurements. These data demonstrate the effectiveness and safety of the intervention process, as well as the potential risks.

**Table 1 tab2:** Secondary outcome measures.

Secondary outcome measure	Assessment time point	Operational definition
Gallbladder volume	7 days post-intervention	Measured by abdominal ultrasound using the ellipsoid formula: Volume = Length × Width × Depth × 0.52
Gallbladder wall thickness	7 days post-intervention	Measured by abdominal ultrasound at the thickest point, accurate to 0.1 mm
Serum total bilirubin	7 days post-intervention	Determined by standard laboratory assay; normal reference range: 3.4–17.1 μmol/L
Post-intervention abdominal pain	7 days post-intervention	Assessed using the Numerical Rating Scale (NRS)^1^; scores range from 0 (no pain) to 10 (worst imaginable pain)
Post-intervention acute pancreatitis	14 days post-intervention	Defined as the presence of characteristic abdominal pain plus serum amylase level ≥3 times the upper limit of normal^2^
Post-intervention gastrointestinal bleeding	14 days post-intervention	Defined as melena (black tarry stools) or a decrease in hemoglobin (Hb) level ≥20 g/L from baseline^3^
Post-intervention nausea, vomiting, and diarrhea	14 days post-intervention	Recorded as the daily frequency of each symptom during the 14-day follow-up period

^1^NRS: Numerical rating scale. A validated self-report pain assessment tool.

^2^Upper limit of normal for serum amylase at our institution: 100 U/L.

^3^Normal reference range for hemoglobin at our institution: 120–160 g/L (female), 130–175 g/L (male).

^4^All ultrasound examinations will be performed by two independent blinded sonographers with ≥10 years of experience in abdominal imaging. All laboratory tests will be conducted using standard methods at the Clinical Laboratory of the First Hospital of Lanzhou University.

Participant timeline please see Figure 2.

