*Stimulation of cholecystokinin (CCK) secretion*: Medium-chain triglycerides (MCTs) are rapidly absorbed in the proximal small intestine, stimulating intestinal I cells to secrete CCK—the primary hormone regulating gallbladder motility. CCK induces strong, coordinated contraction of the gallbladder smooth muscle while simultaneously relaxing the sphincter of Oddi, creating a pressure gradient that facilitates the passage of small stones into the duodenum. Long-chain triglycerides (LCTs) provide a more sustained stimulation of CCK secretion, maintaining gallbladder contractility over an extended period.*Enhanced gastrointestinal motility*: Functional fatty acids promote intestinal peristalsis, which indirectly increases biliary tract motility and accelerates the transit of stones through the common bile duct.*Modulation of bile composition*: Functional fatty acids may alter the lipid profile of bile, reducing cholesterol saturation and inhibiting the further growth of cholesterol stones. In some cases, they may even partially dissolve small cholesterol microliths, making them easier to expel.*Anatomical safety*: The selection of stones <2 mm in diameter ensures anatomical feasibility for passage through the cystic duct (2–3 mm) and common bile duct (6–8 mm), minimizing the risk of biliary obstruction, acute cholangitis, or pancreatitis.

Ultrasound has a high sensitivity for detecting gallstones, but it cannot distinguish between cholesterol and pigment stones solely on the basis of imaging features (26). Therefore, we did not perform relevant analyses on the nature of the stones in this study.

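### The aim of showing that the product alleviates gallbladder inflammation rests on wall thickness alone, analysed within groups, which is not specific evidence on inflammation

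*Protocol article*

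**What the plan says.** Under Secondary objectives, the protocol article names "relevant indices, including the volume of the gallbladder and the thickness of the gallbladder wall" as the indices to be compared before and after treatment, and gives the purpose as "to determine whether the intervention affects gallbladder contraction function and can alleviate gallbladder inflammation".

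The people studied are described in two places. Intervention description requires that a candidate "has no clinical symptoms related to gallstones". Eligibility criteria exclude, among others, "Common bile duct stones, extrahepatic biliary tract stones, or active biliary tract infection" and a history of pancreatitis or cholangitis. Neither section asks for a thickened wall or any other sign of inflammation.

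The scans follow a standard procedure: "Patients will be examined in the supine and left lateral decubitus positions after an 8-h fast".

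On analysis, the Statistical analysis section lists wall thickness, together with volume, as a within-group change from baseline to days 3 and 6. Table 1 instead places both measures at 7 days post-intervention.

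On mechanism, the Discussion expects that "CCK induces strong, coordinated contraction of the gallbladder smooth muscle", with the long-chain component "maintaining gallbladder contractility over an extended period".

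**The concern.** A trial can conclude that a product alleviates inflammation only if it measures something reasonably specific to inflammation, in people who may have some, against a concurrent control. Here the measure is indirect, baseline inflammation is not required, and the listed comparison is before against after within each arm.

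If the wall is thinner after treatment, the article's own wording invites the statement that inflammation was alleviated. If it is thicker, the same wording invites the opposite statement. Neither would follow from the data as planned. At stake is an unsupported mechanistic or therapeutic claim in the trial report. The primary endpoint, the sample size and the decision on efficacy are not affected.

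**Working it through.** The plan states no figure for wall thickness, so there is none to reproduce. The check has four steps.

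**1. Which measure carries the inflammation aim?** Two indices are named. Volume answers the contraction question, which leaves wall thickness. The other measured items do not fill the gap:
- Aims and objectives lists ALT, AST and total cholesterol, presented as markers of liver injury and lipid metabolism.
- Table 1 adds total bilirubin, pain, pancreatitis, gastrointestinal bleeding, nausea, vomiting and diarrhoea.
- The list under Data collection and management adds no inflammatory marker.

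**2. Is there inflammation to act on?** Entry requires freedom from gallstone symptoms and excludes active infection, but sets no minimum wall thickness. Baseline wall thickness is recorded, so the amount of thickening present will be known only after enrolment.

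**3. What contrast does each time point give?**

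| Time point | Experimental arm has had | Control arm has had | Between-arm contrast |
|---|---|---|---|
| Day 3 | 3 days of product | 3 days of placebo | product against placebo |
| Day 6 | 6 days of product | 3 days of placebo, 3 of product | two durations of product |
| 7 days (Table 1) | 6 days of product | 3 days of placebo, 3 of product | two durations of product |

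The last row holds whether the 7 days are counted from the first or the last dose. Only day 3 separates product from placebo, and there the Statistical analysis section lists wall thickness as a within-group change. A within-group change contains any drift over time and any variation between scans. On the latter, the article gives two measurement sites: the anterior wall away from neck and fundus under Standardized ultrasound assessment protocol, and the thickest point in Table 1.

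**4. How far could fasting volume alone move wall thickness?** The documents do not discuss this, so it is a geometric illustration. Assumptions from outside the documents: a spherical lumen of volume V = 20 or 30 mL, a wall of t = 2.0 or 2.5 mm, and wall tissue volume W that stays constant.

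- Inner radius: r = (3V/4π)^(1/3)
- Wall tissue: W = (4π/3)[(r + t)³ − r³]
- After a proportional fall f: V′ = V(1 − f)
- New wall: t′ = [3(V′ + W)/4π]^(1/3) − [3V′/4π]^(1/3)

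Example with V = 20 mL, t = 0.25 cm and f = 0.20: r = 1.684 cm and W = 10.30 mL. Then V′ = 16 mL, the inner radius is 1.563 cm and the outer 1.845 cm, so t′ = 0.282 cm. The wall goes from 2.50 to 2.82 mm, a rise of 0.32 mm.

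Range over the four combinations of V and t:

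| Change in fasting volume | Change in wall thickness (mm) |
|---|---|
| −50% | +0.89 to +1.09 |
| −30% | +0.43 to +0.53 |
| −20% | +0.26 to +0.32 |
| −10% | +0.12 to +0.15 |
| +10% | −0.11 to −0.13 |
| +20% | −0.20 to −0.24 |

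The documents give no expected change in fasting volume, so no row is predicted. The table shows only that a modest shift moves the wall by tenths of a millimetre with no change in tissue.

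**The case against.** The strongest reply is the 8-hour fast. Contraction through cholecystokinin is a response to fat intake, and scanning fasted patients should remove much of the immediate effect of a dose. Read literally, Table 1 may even place the measurement after dosing has ended. This stands as a limit on the filling effect. It does not remove it: the protocol judges contraction function from volume measured under the same fast, so it treats a shift in fasting volume as possible. The article also does not say whether a scan comes before or after that morning's dose.

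A second reply is that the general tests named for continuous variables (independent-samples t-test, Mann–Whitney) compare groups, so a between-arm comparison might be intended. The specific entry for wall thickness is nevertheless within-group.

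Three stronger readings are tempting, and the documents do not support them:
- A reader might infer that the result would mislead in either direction. Under the protocol's own mechanism the filling effect runs one way, towards a thicker wall, and so works against a false finding of alleviation. A thinner wall with a smaller volume would not be explained by filling.
- A reader might infer that large falls in volume are expected at the scans. No section gives a figure for fasted scans.
- A reader might infer that there is no inflammation to alleviate. The exclusions cover infection, pancreatitis and cholangitis. They do not name cholecystitis, and absence of symptoms does not establish a normal wall.

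**Conclusion.** The point holds as one of specificity. Wall thickness alone, in symptom-free people with no inflammation required at entry and analysed as a within-group change, is not specific evidence that the product alleviates inflammation. It would be too strong to say that wall thickness can never inform the question: volume from the same scans allows the two to be read together.

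The lack of any other inflammation measure, the entry rules, the within-group analysis and the timing all follow from the article's text. Only the filling argument rests on assumptions. Under those, a shift of 10% to 20% in fasting volume corresponds to about 0.1 to 0.3 mm of wall. If fasting volume did not change at all, the filling argument would fall away, but time and measurement variation would remain, and so would the lack of specificity. This is a secondary aim, and no primary result depends on it.

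**What to change.** 1. Secondary objectives: delete the closing clause about inflammation, or reword it as *change in gallbladder wall thickness*.
2. Statistical analysis: replace the within-group comparison of wall thickness with a between-arm comparison at day 3, the only product-against-placebo time point. Use either the change from baseline or the day 3 value with the baseline value as covariate.
3. Report gallbladder volume from the same scans beside wall thickness, for description. It should not be an adjustment covariate: it is measured after randomisation and may itself be changed by the product, so adjusting for it would not give a clean between-arm effect.
4. Add day 3 to the wall thickness entry in Table 1, and reconcile the two measurement sites, so that the measure matches the analysis.

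The cost is wording. Day 3 scans, baseline wall thickness and volume are already planned. The sponsor gives up the inflammation claim, which the planned measurements could not have supported.

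### The objective on gallbladder contraction function rests on fasting volume and wall thickness only, which cannot by themselves establish an effect on contraction

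*Protocol article*

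**What the plan says.** All references are to the protocol article.

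- **Secondary objectives.** Patients are compared by ultrasound before and after the intervention on "relevant indices, including the volume of the gallbladder and the thickness of the gallbladder wall". The stated purpose is to "determine whether the intervention affects gallbladder contraction function and can alleviate gallbladder inflammation".
- **Standardized ultrasound assessment protocol.** One protocol governs all ultrasound examinations: "Patients will be examined in the supine and left lateral decubitus positions after an 8-h fast". Five measurements are standardized: stone number, maximum stone diameter, stone volume, gallbladder volume and wall thickness.
- **Secondary outcome measures, Table 1.** Gallbladder volume is a single static quantity: "Measured by abdominal ultrasound using the ellipsoid formula: Volume = Length × Width × Depth × 0.52". Its time point is 7 days post-intervention.
- **Statistical analysis.** Changes in gallbladder volume and wall thickness are to be compared within each group, from baseline to days 3 and 6.
- **Intervention description.** Experimental patients "take 50 mL of oral functional fatty acids on an empty stomach every morning for 6 consecutive days". The section sets scans on the 3rd and 6th days but does not time any scan to a dose.
- **Discussion.** The proposed mechanism starts from a fat stimulus that releases cholecystokinin: "CCK induces strong, coordinated contraction of the gallbladder smooth muscle".

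**The concern.** The article's own mechanism treats contraction as a response: fat is swallowed, cholecystokinin is released, and the gallbladder empties. Measuring that response needs a volume before the stimulus and another after it. The plan describes only volumes taken in the fasting state, on different days. A difference between two such volumes is a difference in resting volume.

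What is at stake is how a secondary result is read. Trial design and Discussion both explain the expected benefit through gallbladder motility. A shift in fasting volume could therefore be reported as confirming that mechanism, and an unchanged fasting volume as showing no effect on contraction. Neither conclusion would follow from the data. The planned within-group analysis adds to the problem, because a before-and-after change in one arm does not isolate an effect of treatment.

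**Working it through.** The article gives no figure for contraction, so there is none to reproduce. The check has three steps.

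**1. Objective against measurement**

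| Element | What is stated | Does it measure emptying? |
|---|---|---|
| Objective | Effect on contraction function | This is the target |
| Indices named | Volume, wall thickness | No |
| State at examination | 8-hour fast, all examinations | No stimulus specified |
| Table 1 definition of volume | One ellipsoid volume | No paired volume |
| Planned analysis | Change between visits, within group | No same-day pair |

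None of the measurement or analysis sections adds an emptying index.

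**2. Does fasting volume determine emptying?**

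Write Vf for fasting volume and Vp for volume after a stimulus. The ejection fraction is

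EF = (Vf − Vp) / Vf.

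The plan describes Vf only. The volumes below are assumptions for illustration and do not come from the article.

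Same fasting volume, different contraction (Vf = 25 mL):
- Vp = 20 mL: (25 − 20)/25 = 20%
- Vp = 15 mL: (25 − 15)/25 = 40%
- Vp = 10 mL: (25 − 10)/25 = 60%
- Vp = 5 mL: (25 − 5)/25 = 80%

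Different fasting volume, same contraction:
- Vf = 20 mL, Vp = 10 mL: (20 − 10)/20 = 50%
- Vf = 30 mL, Vp = 15 mL: (30 − 15)/30 = 50%

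So contraction can differ while fasting volume stays the same, and fasting volume can differ while contraction stays the same.

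**3. Which contrast could show a treatment effect on fasting volume?**

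| Time | Experimental arm has received | Control arm has received |
|---|---|---|
| Day 3 | 3 days of oil | 3 days of placebo |
| Day 6 | 6 days of oil | 3 days of placebo, then 3 days of oil |
| Table 1 (7 days post-intervention) | Oil | Placebo, then oil |

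Only the between-arm comparison at day 3 sets oil against placebo. Trial design itself says that day 6 compares two durations of active treatment.

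**The case against.** The strongest reply is that the defect is one loosely worded sentence. Contraction function is not a defined outcome, hypothesis or test. Aims and objectives does not mention it, Table 1 lists volume and wall thickness under their own names, and the Discussion calls the mechanism only a possible one. This stands, and it limits the weight of the point. A reader might infer that following the plan must produce a conclusion about contraction. The documents do not go that far; they state the purpose and supply no measurement that serves it.

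A second reply is that the list of indices is open-ended, the participant timeline figure is not available here, and the order of dose and scan on a given morning is not stated. A reader might infer that no scan could ever follow a dose. The text does not settle that, although an 8-hour fast most naturally excludes a prior oil dose. The point does not depend on it: the fast applies to all examinations, and a single volume taken after a dose, without a same-day volume before it, would still not measure emptying.

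A third reply is that resting volume may carry some information about motility. This also stands. A reader might infer from the arithmetic that fasting volume is wholly unrelated to contraction. Nothing in the documents shows that, and the illustration uses assumed volumes. It shows that fasting volume does not determine contraction, which is all the point needs.

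**Conclusion.** The concern holds in a limited form. The article sets out to determine an effect on contraction function but describes only static volume and wall thickness, with all examinations after an 8-hour fast. A between-visit change in fasting volume is at most an indirect index and cannot alone establish an effect on contraction.

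In the illustration, one fasting volume of 25 mL is consistent with ejection fractions from 20% to 80% over the assumed post-stimulus volumes of 20 to 5 mL. That spread shows non-identifiability and is not an estimate for this trial.

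The conclusion rests on two readings: that the 8-hour fast covers every examination, as the ultrasound section states, and that no emptying measure exists beyond those described. The consequence is confined to a secondary mechanistic objective. The primary endpoint, complete expulsion at day 3, is untouched. The other half of the same sentence, on inflammation, was not examined here.

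**What to change.** 1. In Secondary objectives, restate the purpose as the effect of the intervention on fasting gallbladder volume and wall thickness. Drop the claim about contraction function there and in any conclusion drawn from these measures.
2. In Statistical analysis, replace the within-group comparison of the two measures with a between-arm comparison of change from baseline. Name day 3 as the only placebo-controlled contrast, and describe day 6 as a comparison of treatment durations. The two-sample tests already named in that section for continuous variables can be applied to the change scores.
3. While editing, reconcile the time points for these measures: Table 1 gives 7 days post-intervention, whereas Statistical analysis gives days 3 and 6.

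The cost is a wording change plus a small change to one secondary analysis. No scan, visit or patient is added. The trial gives up a mechanistic claim; keeping that claim would require paired fasting and post-stimulus volumes, which the article does not describe.
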